The PPI group suggested that they would be willing to wait at least 6 months for laser intervention but would not be willing to forego treatment entirely. There are ethical concerns regarding completely depriving patients of PDL as this is part of “standard” burns care at some sites. Similarly, recruitment to the trial would be difficult if the alternative to not being in the trial was to be given PDL treatment.

Finally, there is the issue of loss of patients to follow-up as a result of waning compliance if they have a positive result with PDL intervention; attrition of patients in longitudinal burns studies is a common issue which can confound trials^
58
^. The authors have allowed for attrition in our sample size calculation.

Standard interval between treatment sessions for PDL is usually 4 – 6 weeks. The bruising resulting from the treatment subsides within 2 – 3 weeks and the effect of the treatment is evident at this point. For this trial, there is around 3 months between the last treatment and measurement of outcome at the primary end-point. This primary endpoint therefore allows a reasonable duration of time for laser treatment to have an observed effect.

It is acknowledged that this is a relatively short follow-up period given that the duration of scar maturation can take upwards of 2 years. A longer-term outcome than 6 months would prove interesting, but the authors hypothesise that a shorter-term improvement would serve to “flatten the curve” of scar maturation, expedite the scarring process and eventually lead to an improved scar outcome. Even at this time point, this may translate as a clinical efficiency and saving for the NHS by a reduction in follow-up appointments and cost of further scar revision; thus justifying the study from the perspective of clinical efficiency.

The 6 month follow-up strikes a compromise between reliable data on scar outcome and a suitable residual size of cohort from which to draw reliable conclusions. It is also a compromise between ensuring a reasonably long follow-up for treatment to show effect and having a research design that was acceptable to potential participants. It is concluded that having a 6 month follow-up is long enough to show any benefits of PDL, but short enough to counter ethical and recruitment concerns.

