### Participant timeline

Each participant attends the site for assessment at four study sessions and the primary end-point is at 6 months follow-up (Table 2).

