### Data collection

#### Blinding (masking)

Blinded assessments of observer-rated POSAS and colour measurement are performed by scar management HCPs prior to ± laser treatment. The participants are instructed not to divulge their allocation to HCP to maintain blinding. This means that both the observer-rated POSAS and colour measurement are conducted by someone blinded to treatment allocation.

The patient-rated POSAS (primary outcome) and the relevant QoL questionnaires are completed by the participant. Although this assessment cannot be blinded, it was felt, as informed by the PPI group, that the participant’s perspective should be paramount in this trial. It is accepted that this may bias the patient-rated POSAS result in that they will make their rating knowing to which treatment arm they had been allocated. However, blinded clinician-rated secondary outcomes are included. In addition, the data collection, statistical analysis and initial interpretation of the primary and secondary outcome results will be blinded.

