#### Harms

The most serious adverse event in the use of a laser is retinal burn, which may lead to permanent blindness. All laser clinics/sites are subject to government guidelines. The Health and Safety at Work Act 1974 and the Management of Health and Safety at Work Regulations 1999 require the employer and employee to undertake reasonable and practical health and safety measures. This serves to minimise this risk though designation of a “Laser Controlled area”, as defined by the Control of Artificial Optical Radiation at Work Regulations (AOR) 2010, performance of a risk assessment, publication of local rules and use of Personal Protective Equipment. There are no necessary regulatory approvals. All laser sites in the study have appropriate laser safety precautions in place, as determined by the local Laser Protection Advisors.

The adverse events from PDL treatment include, but are not limited to:

BlistersScabbingExcessive oedemaExcessive pigmentation changesExcessive PainWorsening of the scarOther

The scar might be fragile at this early stage but blistering is unlikely. Redness and/or oedema are to be expected and usually resolve within 7 – 10 days. Changes in pigmentation are often caused by the burn injury and the subsequent scarring; hypopigmentation is often inevitable in burn scarring. Hyperpigmentation resolves or can be treated at a later stage using Q-switched lasers. There have been few documented occurrences of worsening of the scar using PDL.

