### Retention

All attempts will be made to collect all outcome measures on all participants, regardless of whether they adhered to their treatment. Outcome measures are collected at clinic appointments that form part of their usual care and so it is anticipated that retention will be good. The study design has allowed for up to 20% of participants not to supply data within the sample size considerations.

If a participant does not attend their clinic appointment, this will be rearranged within the next couple of weeks. If this does not happen, attempts will be made to collect those outcome measures that can be collected by phone, prioritising the collection of the primary outcome. If it is not possible to collect data then, where possible, the reason why will be recorded to help with populating the CONSORT flow chart.

Participants in the laser arm of the trial will receive three treatment sessions. A record of attendance at treatment sessions will be kept, and whether they actually received the treatment. If they didn’t receive treatment, the reason why will be recorded, where available.

In consideration of the current COVID crisis, further consideration is made as to the conduct of the study. The primary outcome of patient-rated POSAS can be obtained over the phone when the patient is unable to attend. The observer-rated POSAS can be performed using photos; though this is less reliable particularly for evaluation of thickness and pliability. Patient photographs are also not generally of a sufficient standard. Similarly, the healthcare resource data, patient perception question and qualitative interview can be performed by telephone. Most standard care treatments can be managed remotely, whereas the laser treatment and colour measurement would require the attendance of the patient.

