### Interventions

#### Pulsed Dye Laser (treatment arm)

There are two models of PDL from different manufacturers; Cynergy (Cynosure, West-ford, MA, USA) and the Vbeam (Syneron Candela, USA). The settings to be used are:

10 mm, spot size0.5 ms, pulse duration5 – 9 J cm^-2^, energy fluenceApprox. 10% overlapSingle pass

Laser treatment follows assessment and is performed by a trained laser operator. Where multiple scars are present, the laser operator treats the study scar. Other non-contiguous scars may be treated within the limit of total treated area deemed suitable. The energy is selected to produce a degree of purpura during treatment without the presence of skin blanching. The skin response is instantaneous and should be dark purple to black. Blanching (or whitening) in the treatment area suggests over-treatment and is to be avoided. If the operator is unsure, a pause of up to a couple of minutes can be adopted to verify the skin response. Once the desired response is observed, the operator should treat the entire trial scar.

Skin cooling is administered during the treatment. Almost all patients cope with the pain without any anaesthesia; neither topical nor local. The PPI group agreed that pain, though sensate, is not an issue. If necessary, topical anaesthesia is offered and recorded, if used. This provides comfort for the participant and minimises collateral damage. Post-treatment photographs are taken after treatment. Cool Aloe Vera gel may be offered to the participant to apply to the treated area after treatment and its application will be recorded. This may help to soothe any discomfort and reduce the residual heat. The treated areas do not require dressing and after-care information is provided. The patient is advised to avoid perfumed cosmetics, any abrasive drying, tight-fitting clothes, and any strenuous exercise or swimming in chlorinated water for 72 hours. This will include the use of any pressure garments.

At subsequent visits, the participants are asked to report on any adverse effects of the treatment. The previous settings should be used to start the treatment but the operator may increase the energy in 0.5 Jcm^-2^ steps until a similar response to the previous visit is achieved. All laser settings are recorded for each visit.

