#### Standard care (control arm)

Both arms of the trial will be given standard care. The choice of standard care for this trial includes; moisturisation and massage up to 2 – 3 times per day (as directed by the HCP; where maintenance of hydration is required) ± silicone gel treatment ± pressure garments, dependent upon scar maturation.

The control arm receives standard care only. The treatment arm receives a course of three PDL treatments at intervals of 6 weeks, in addition to standard care treatment, as detailed in Table 2. All follow-ups allow ± 1 week to allow for clinic administration.

The following treatments are not permitted for the study scar only and will mean that the participant is withdrawn from the study: Fractional ablative laser, micro-needling, scar revision and/or grafting.

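### The scheduled enquiry about laser harms comes about 6 weeks after sessions 1 and 2 and 14 weeks after session 3, so short-lived reactions rest on recall; at week 26 the enquiry is not kept apart from the blinded assessor

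*Protocol article*

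**What the plan says.** The harms enquiry is described in the intervention section for the laser arm: "At subsequent visits, the participants are asked to report on any adverse effects of the treatment". The article does not say who asks.

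The schedule comes from three places. Standard care (control arm): "The treatment arm receives a course of three PDL treatments at intervals of 6 weeks". Participant timeline: "Each participant attends the site for assessment at four study sessions and the primary end-point is at 6 months follow-up"; Table 2 puts those sessions at weeks 0, 6, 12 and 26. On windows: "All follow-ups allow ± 1 week to allow for clinic administration".

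Two durations are given. Harms: "Redness and/or oedema are to be expected and usually resolve within 7 – 10 days". Follow-up duration: "The bruising resulting from the treatment subsides within 2 – 3 weeks and the effect of the treatment is evident at this point".

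Blinding (masking) says that observer-rated POSAS and colour are assessed by blinded scar-management staff before any laser treatment at the visit. It adds: "The participants are instructed not to divulge their allocation to HCP to maintain blinding". Data management allows research nurses, principal investigators or the scar assessor to collect data, with site variation set out in SOPs.

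Secondary objectives include the adverse-effect profile of the laser. The three sections on harms reporting send all adverse events to the Chief Investigator, have non-serious ones written in the participant's notes, and require a form for serious ones within 24 hours.

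**The concern.** Harms lists blisters, scabbing, excessive oedema and excessive pain. Reactions of this kind can come and go between visits. If participants are first asked weeks or months later, mild and resolved events are easily forgotten, placed at the wrong session or thought not worth mentioning. The error would tend to run one way, towards a more favourable harms profile, and would be largest for the third session.

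Week 26 raises a second issue. At weeks 6 and 12 the laser operator sees the participant after the blinded assessment and can ask then. At week 26 no laser session is scheduled, and the assessor is among those who may collect data. The enquiry concerns effects of the laser, so an answer given to the assessor could disclose the arm just when observer POSAS and colour are rated. Blinding (masking) offers the blinded clinician-rated outcomes as the balance to a patient-rated primary outcome that cannot be blinded, so their blind is worth protecting.

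**Working it through.** **Inputs**
- Laser sessions: three at 6-week intervals, hence weeks 0, 6 and 12 (Standard care; Table 2 time points).
- Visits: weeks 0, 6, 12 and 26 (Participant timeline; Table 2).
- Window: ±1 week per follow-up (Standard care).
- Usual resolution: redness and oedema 7–10 days (Harms); bruising 2–3 weeks, i.e. 14–21 days (Follow-up duration).

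**Step 1: reproduce the article's own interval.** Follow-up duration puts the last treatment around 3 months before the primary end-point. From the schedule, 26 − 12 = 14 weeks = 98 days, and 98 / 30.44 = 3.2 months. The figures agree, so the session timing is read correctly.

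**Step 2: gap from session to next scheduled enquiry** (next visit − session)
- Session 1: 6 − 0 = 6 weeks = 42 days
- Session 2: 12 − 6 = 6 weeks = 42 days
- Session 3: 26 − 12 = 14 weeks = 98 days

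**Step 3: time from usual resolution to enquiry** (gap − resolution time)

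| | Redness/oedema | Bruising |
|---|---|---|
| Sessions 1 and 2 | 42 − 10 = 32 to 42 − 7 = 35 days | 42 − 21 = 21 to 42 − 14 = 28 days |
| Session 3 | 98 − 10 = 88 to 98 − 7 = 91 days | 98 − 21 = 77 to 98 − 14 = 84 days |

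**Step 4: effect of the windows.** If both visits move by a week, a 6-week gap becomes 4 to 8 weeks and the 14-week gap becomes 12 to 16 weeks. In the most favourable case:
- Sessions 1 and 2 (28 days): 28 − 10 = 18 days after redness/oedema and 28 − 21 = 7 days after bruising.
- Session 3 (84 days): 84 − 10 = 74 days after redness/oedema and 84 − 21 = 63 days after bruising.

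Even then every scheduled enquiry falls after usual resolution. Third sessions, with the longest gap, are one in three of those planned.

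**Step 5: do other provisions close the gap?** The harms-reporting sections say what staff do once they know of an event. They set no contact or prompt between visits that would bring a mild, self-limiting event to their notice. Retention names what can be collected by telephone: the primary outcome and, in addition, "Similarly, the healthcare resource data, patient perception question and qualitative interview can be performed by telephone". Harms are not named there.

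**The case against.** The case on the other side has five parts.

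1. **Other routes exist.** All adverse events go to the Chief Investigator, with no tie to a visit, so a participant who telephones about a blister is covered. The operator also watches the immediate skin response, and photographs are taken after treatment. This stands: the visit question is the only scheduled enquiry but not the only way a harm can become known.

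2. **The durations fit only part of the list.** The 7–10 days applies to redness and oedema that are expected, and the 2–3 weeks to bruising, where purpura is the intended response. No duration is given for blisters, scabbing or pain. Pigmentation change and worsening of the scar may last and can still be detected at later visits. This stands, and it confines the point to short-lived reactions.

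3. **The loss of blinding is not documented.** A reader might infer that third-session harms must either be lost or break the blind. The article does not support that. Nowhere does it say that the blinded assessor asks about harms. Under Concealment mechanism the principal investigator and the treating professional know the allocation, and either of them, or another nurse, could ask once the assessment is done. The instruction not to disclose allocation protects the assessor; it does not stop a report to someone else. What remains is a risk, because the assessor may collect data and no separation is stated.

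4. **An article leaves such detail to SOPs.** This is fair for who asks and on which form. It does not reach the timing, which the article states and which sits poorly with its own resolution times.

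5. **The telephone list is a contingency and not exhaustive.** It also leaves out CARe and SF-12. This stands, so the omission of harms there is minor.

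**Conclusion.** The point holds as a cheap improvement to how harms are ascertained. As scheduled, solicited short-lived reactions depend on recall about 6 weeks after sessions 1 and 2 and about 14 weeks (12 to 16 with windows) after session 3. Under-reporting of these events is likely but not certain, since resolved events can be remembered or reported spontaneously.

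The intervals rest only on the stated schedule. The statement that effects have gone by then rests on the article's usual resolution times and is shown only for redness, oedema and bruising; applying it to blisters, scabbing or pain is an assumption. A percentage for the shortfall is tempting but would only restate an assumed recall rate, because the documents give no figure for recall or for event frequency.

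The blinding issue is conditional. It arises at week 26 if the assessor makes the enquiry, or hears the answer, before rating. It would then affect observer POSAS and colour. The primary outcome is patient-rated and unblinded in any case.

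**What to change.** - Give participants in both arms a one-page self-completed adverse-event card listing the items under Harms, to fill in during the 3 weeks after each of the week 0, 6 and 12 visits. Three weeks matches the upper end of the stated resolution time for bruising. Using the card in both arms keeps the form from revealing allocation and gives a comparison for events that the burn itself can cause, such as pigmentation change.
- Have cards returned to unblinded site staff or the trial coordinator, not to the scar assessor.
- At week 26, put the same items in the questionnaire pack, sealed from the assessor, or ask them only after observer POSAS and colour are complete.
- Add harms to the items in Retention that can be collected by telephone.

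The cost is one printed page, a little extra data entry, slight participant burden and some unreturned cards. Treatment, visits and sample size do not change.

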#### Standard care (control arm)

Both arms of the trial will be given standard care. The choice of standard care for this trial includes; moisturisation and massage up to 2 – 3 times per day (as directed by the HCP; where maintenance of hydration is required) ± silicone gel treatment ± pressure garments, dependent upon scar maturation.

The control arm receives standard care only. The treatment arm receives a course of three PDL treatments at intervals of 6 weeks, in addition to standard care treatment, as detailed in Table 2. All follow-ups allow ± 1 week to allow for clinic administration.

The following treatments are not permitted for the study scar only and will mean that the participant is withdrawn from the study: Fractional ablative laser, micro-needling, scar revision and/or grafting.

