^. One theory is that this aberrant vasculature provides a ready route for successive waves of inflammatory cells to enter the early scar. PDL targets this vasculature specifically with relatively little collateral injury. In doing so, it is suggested that PDL is effective for reduction of both scar redness and itch but moreover, it may limit the tendency for late fibroblast ingress and proliferation with the production of localised, excessive scar tissue, such as collagen. Simplistically, PDL devices may be preventative of later increases in scar thickness and density.

AFL works inherently to destroy tissue by vaporisation in a highly localised spatial orientation. In doing so, they reduce bulk, thickness and stiffness of scars. Early HBS may not have these facets and as such, there is still debate about the utility of AFL devices early in HBS maturation. Moreover, the relatively greater energy levels associated with AFLs may cause more collateral injury including immediate inflammation^
41
^ and be associated with more ‘down time’ for the patient.

There are several notable papers that acknowledge that each has their merit and suggested algorithms for laser treatment of burn scars may include both; but with an emphasis seemingly of choosing PDL as the first line^
42–45
^. The authors acknowledge that future algorithms for laser treatment of more problematic scars might involve the AFL devices, particularly where there are significant issues with thickness, density or pliability. The authors also note that there is a concurrent study for the use of Carbon Dioxide AFL for the treatment of HBS in the UK that is being funded by the Scar Free Foundation.

Prior to the evolution of carbon dioxide AFL, a high-quality systematic review stated that “the PDL 595 nm is promising, although more research is necessary. Future research, with a low risk of bias, well-defined scar characteristics, validated outcome measures, standardized measurement methods, follow-up periods of at least 6 months and well-defined laser settings, is needed”^
46
^.

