### Statistical methods

#### POSAS (Version 2)

Participants are analysed in trial arm they were initially randomised to regardless of whether treatment was completed (intention-to-treat analysis). Significance tests are 2-sided at the 5% level. Patient component of the POSAS scale at 6 months is the primary outcome measure. In the main analysis, mean POSAS scores at 6 months is compared between trial arms using multiple regression with treatment arm, study site (a design variable) and burn location (a stratification variable coded as (1) head/neck, (2) torso or (3) limbs) as factors and baseline patient POSAS and current age as co-variates. A similar approach will be used for secondary outcome analyses.

For the primary outcome, additional analysis will:

consider patient POSAS over all 4 time points (baseline, 6 week, 12 week and 6 months) using a multi-level/mixed model.use multiple imputation to assess the impact of missing data.conduct per-protocol and Complier-Average Causal Effect (CACE) analyses based on completion of the 3 laser sessions.

Prior to the completion of data collection, a detailed statistical analysis plan will be developed and signed off by the CI and TSC.

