#### Analysis population and missing data

The main analysis will analyse participants in the group to which they were randomised, regardless of the treatment they actually received. No imputation of missing data will be used for the main analyses, but multiple imputation of missing data will be conducted in additional analyses for the primary outcome. Further details of the approach to be used will be described in a detailed statistical analysis plan

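### Withdrawing participants from the study after a non-permitted scar treatment conflicts with the intention-to-treat analysis and can bias the primary comparison in either direction

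*Protocol article*

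**What the plan says.** The protocol article, Interventions, Standard care (control arm), names four procedures ("Fractional ablative laser, micro-needling, scar revision and/or grafting") that are "not permitted for the study scar only and will mean that the participant is withdrawn from the study". The sentence speaks of leaving the study, not of stopping trial treatment, and it applies to both arms.

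Three other places point the other way:

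- Statistical methods, POSAS (Version 2): "Participants are analysed in trial arm they were initially randomised to regardless of whether treatment was completed".
- Analysis population and missing data: the main analysis groups participants as randomised, "regardless of the treatment they actually received". The same section adds: "No imputation of missing data will be used for the main analyses".
- Retention: "All attempts will be made to collect all outcome measures on all participants, regardless of whether they adhered to their treatment".

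Multiple imputation and a mixed model over the four POSAS time points are planned for the primary outcome, but only as additional analyses.

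**The concern.** Receiving a non-permitted procedure is a departure from assigned treatment, which is what an intention-to-treat rule is meant to absorb. Here a protocol rule, rather than the patient, ends follow-up, and it does so because of something that happened after randomisation.

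The participants affected are unlikely to be a random subset. The Introduction (Laser treatment) says that "future algorithms for laser treatment of more problematic scars might involve the AFL devices", so at least one of the four procedures is tied to worse scars. The rate may also differ by arm: patients know their allocation (Blinding), and controls are offered laser only when their participation ends (Follow-up duration). If the rates or the severity of those removed differ between arms, the main analysis compares two groups that are no longer the randomised ones.

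A later statistical analysis plan cannot undo this. Once a site stops follow-up, the week-26 score does not exist.

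**Working it through.** **1. The passages side by side.** Suppose a participant has one of the four procedures on the study scar at week 16. Under Standard care (control arm) the site withdraws the participant. Under Retention the site should still seek every outcome. Under the two analysis sections the participant belongs in the main analysis, but with no week-26 score and no imputation contributes nothing to it. A site cannot follow both rules.

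**2. The plan's own figure.** Inputs from Sample size: difference 6, SD 10, two-sided 5%, power 90%.

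- n per arm = 2 × (1.960 + 1.282)² × (10/6)² = 58.4, so 59 by the normal approximation. The t-test gives 59.4, so 60.
- Power with 60 per arm is 0.903 (t-test).
- Allowing for 20% drop-out: 120 / 0.8 = 150.

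The stated 60, 120 and 150 reproduce and are not in dispute.

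**3. Bias formula.** Let p be the share of an arm withdrawn and D the number of points by which the withdrawn score worse than those retained in the same arm. The whole-arm mean is the retained mean + p × D, so the retained mean is too low (too good) by p × D. With the benefit written as control minus laser:

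retained difference = all-randomised difference − (pC − pL) × D, where D = g × SD.

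**4. SD.** Sample size gives follow-up SDs of 11.2 (15 patients) and 11.5 (46 scars). Pooled: √[(14 × 11.2² + 45 × 11.5²) / 59] = 11.43.

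**5. Results.** The values of pC, pL and g are assumptions; the documents give none.

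| Controls v laser withdrawn | g | Bias in points | Share of 6 |
|---|---|---|---|
| 5% v 2% | 0.5 | 0.03 × 0.5 × 11.43 = 0.17 | 3% |
| 10% v 3% | 1.0 | 0.07 × 1.0 × 11.43 = 0.80 | 13% |
| 15% v 5% | 1.5 | 0.10 × 1.5 × 11.43 = 1.71 | 29% |

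All three rows assume that controls lose more, so the bias is toward no effect. Swapping the rates between arms reverses the sign.

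**6. Direction and power.** These use the plan's SD of 10, a true difference of 6, and 60 per arm before withdrawals. Power = Φ(retained difference / SE − 1.96), with SE = 10 × √(1/nC + 1/nL).

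| Controls v laser withdrawn | D (points) | Retained difference | Power |
|---|---|---|---|
| 5% v 5% | any, same in both arms | 6.00 | 0.89 |
| 10% v 5% | 10 | 5.50 | 0.83 |
| 10% v 0% | 10 | 5.00 | 0.76 |
| 10% v 0% | 15 | 4.50 | 0.67 |
| 0% v 5% | 15 | 6.75 | 0.95 |

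Equal rates with equal D cost a little power but cause no bias. The last row's higher power is not a gain, because it comes from an inflated difference.

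**The case against.** The strongest reply is that *withdrawn* is loose wording for stopping trial treatment, since Retention and the analysis sections already commit to following everyone. The article also condenses a fuller protocol. If that is the intention, the harm disappears. But the sentence says otherwise, and Retention makes no reference to it, so the text still needs reconciling.

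Several further objections stand and limit the point:

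- **Frequency.** These procedures may be uncommon before week 26. Scar assessment steers selection of the study scar away from areas likely to need surgery, and the Introduction calls the use of ablative laser in early scars still debated.
- **Who is removed.** A reader might infer that the rule removes treatment failures and therefore biases toward no effect. The documents do not say that. Revision or grafting can have other reasons, such as contracture, and the direction depends on which arm loses more.
- **Repair.** A reader might infer that multiple imputation cannot help. That is too strong. POSAS is also taken at weeks 6 and 12 (Table 2), and imputation and the mixed model can use those scores. If escalation follows severity already recorded, much of the loss could be recovered. Both are additional analyses, however, and neither sees what happened after the last recorded score. Baseline adjustment in the main analysis also removes part of any severity visible at entry; the figures above ignore this.
- **Drop-out allowance.** A reader might infer that the rule uses up the 20%. With 75 recruited per arm, 10% and 3% are 7.5 + 2.25, or about 10 of the 30 losses allowed for. The allowance protects numbers, not against loss related to outcome.
- **What is recovered.** Week-26 scores collected after a procedure may reflect that procedure. For an intention-to-treat contrast the relevant D is the score actually reached at week 26, which could differ from the values assumed here.

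**Conclusion.** The conflict is established by the text alone. Taken literally, the withdrawal rule is a post-randomisation exclusion that the main analysis, without imputation, carries straight into the primary comparison, contrary to the intention-to-treat and retention statements.

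The size of any bias is not established. About 0.8 points, with a range of 0.17 to 1.7, rests on assumed withdrawal rates, an assumed gap between withdrawn and retained participants, and no credit for baseline adjustment. The bias can go either way, and is nil if the arms lose equal shares of equally worse participants. The case for acting rests on the contradiction and on the fact that an uncollected score cannot be recovered, not on any one of these figures.

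**What to change.** Reconcile Standard care (control arm), Retention, POSAS (Version 2), and Analysis population and missing data. Replace withdrawal from the study with a rule along these lines:

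- Receipt of a listed treatment on the study scar, and its date, is recorded as a protocol deviation.
- Follow-up continues, and all week-26 outcomes are collected and analysed as randomised.
- Such participants are excluded only from the per-protocol analysis. Its present definition rests on completing three laser sessions, so it needs this added.
- Withdrawal from the study is reserved for participants who withdraw consent to data collection.

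This concerns data collection and analysis only. It leaves open which treatments are permitted and whether trial treatment continues after one of them.

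The cost is a short protocol change and one case report form field. There are no extra visits, because week 26 is already scheduled and Retention allows the primary outcome to be taken by telephone. The sample size of 60 per arm, 120 analysable and 150 recruited is unchanged.
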